### Outcomes and instruments

#### Sample characteristics

General patient characteristics such as age, handedness, educational level and use of medication will be assessed. Furthermore the digit span of the Wechsler Adult Intelligence Scale (WAIS) will be used to determine working memory capacity [26]. In addition the Dutch Version of the Adult Reading Test (NLV) will be used to assess premorbid intellectual functioning [27]. The Mini International Neuropsychiatric Interview (MINI) [28] will be used to determine whether the participant has any psychiatric DSM-IV diagnoses. The substance use during life questionnaire from the measurement in the addictions for triage and evaluation (MATE) [29] will be used to assess lifetime drug use. For a comprehensive assessment of the alcohol use history an adapted version of the life time drinking history [30] will be used.

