#### Primary outcome measure

The primary outcome of the study will be the abstinence rate after the add-on HF-rTMS treatment (in line with the guidelines of the European Medicines Agency [31]). This will be defined as the number of abstinent days in the 180 days after the last stimulation session measured using the Time Line Follow Back (TLFB) [32] at six months follow up.

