#### Secondary outcome measures

The secondary outcome measures of the study will be described below.Total alcohol consumption after the add-on HF-rTMS treatment. This amount (g) of alcohol will be calculated using the TLFB at three months and six months follow-up.Days until the first relapse after the add-on HF-rTMS treatment, wherein relapse is defined as a heavy drinking day. This holds more than 60 g alcohol per day for men and more than 40 g alcohol per day for women [31, 33]. This measure will be assessed using the TLFB at three months follow up and six months follow-up. Individuals who do not relapse will receive the highest score of 90 days.Change in craving levels after the add-on HF-rTMS treatment will be measured using the Alcohol Urge Questionnaire (AUQ) [34] assessed after the last session of the add-on HF-rTMS treatment, at three and six months follow-up.

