##### Questionnaires

Questionnaires that will be filled in during the study are:Alcohol consumption burden measured with the Alcohol Use Disorders Identification Test (AUDIT) [36].Confidence in abstaining from drinking as measured with the Alcohol Abstinence Self Efficacy (AASE) [37].Depressive symptoms as measured with The Beck Depression Inventory (BDI) [38].Impulsive behavior will be assessed using Barratt Impulsivity Scale-11 (BIS) [39], UPPS (urgency, premeditation, perseverance, sensation seeking) [40] and Behavioral inhibition and Behavioral Activation systems (BIS/BAS) [41] questionnaires.Current state anxiety as measured with the state trait anxiety inventory (STAI STATE) [42].Experience of positive and/ or negative affect measured with the Positive And Negative Affect Scale (PANAS) [43].

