#### Descriptive statistics

Descriptive analyses will be performed in order to see whether randomization resulted in two research groups with a similar distribution of demographic factors. Appropriate parametric and non-parametric statistical tests will be used to analyze descriptive statistics, and if required, multiple comparison corrections will be performed.

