#### Primary outcome measure

Data of the primary outcome measure will be analyzed in accordance with the intention-to-treat principle. Missing data of subjects that are randomized and received at least one stimulation session will be imputed in order to achieve complete datasets. Subsequently an appropriate test for comparing two groups will be used depending on the distribution of the outcome measure. Additionally, data of the primary outcome measure will be analyzed with only treatment completers (according to the per protocol analysis), again using an appropriate test depending on the distribution of the outcome measure.

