#### Secondary outcome measures

An appropriate test for comparison of two groups will be used depending on the distribution of the outcome measures ‘days until first relapse’ and ‘total alcohol consumption’.

Multilevel models (capable of handling missing data points) with predictors time, treatment and time X treatment interaction will be used to test for the effect of the HF-rTMS add-on treatment on craving. The following time points will be included: post HF-rTMS, 3 months follow up and 6 months follow up.

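### The comparisons of abstinent days and total alcohol leave out the drinking measures taken on test day 1, at the cost of some precision (size uncertain, possibly small) but no bias

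*Protocol article*

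**What the plan says.** **Outcomes.** The primary outcome is abstinent days: "This will be defined as the number of abstinent days in the 180 days after the last stimulation session". For total alcohol consumption, a secondary outcome: "This amount (g) of alcohol will be calculated using the TLFB at three months and six months follow-up".

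**Analysis.** Under Statistical analyses, Primary outcome measure, missing data are imputed and then: "Subsequently an appropriate test for comparing two groups will be used depending on the distribution of the outcome measure". Under Secondary outcome measures, total alcohol consumption is treated alike: "An appropriate test for comparison of two groups will be used depending on the distribution of the outcome measures". Neither sentence names a covariate. The models for craving, questionnaires and neurocognitive measures, by contrast, list their predictors (time, treatment and their interaction).

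**Baseline data on drinking.** Under Sample characteristics: "For a comprehensive assessment of the alcohol use history an adapted version of the life time drinking history [30] will be used". Table 1 marks this history on test day 1, and marks the AUDIT, which the Questionnaires section presents as a measure of the burden of alcohol consumption, on test day 1 and at 12 months. The TLFB is marked only at 3, 6 and 12 months.

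**Design.** Under Inclusion procedure, randomisation is stratified by anti-craving medication and age. The only stated use of baseline comparisons is descriptive: "Descriptive analyses will be performed in order to see whether randomization resulted in two research groups with a similar distribution of demographic factors".

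**The concern.** Both outcomes measure drinking after treatment, and the trial records drinking before treatment. If earlier drinking predicts later drinking, part of the spread in the outcome can be explained by data the trial already has, and a plain two-group test leaves that part in the error term. Drinking severity is not a stratification factor, so the design does not remove it either.

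This matters more than usual here because, by the Power analysis section's own account, the sample size does not come from the primary outcome. It starts from 30 in the active group of an earlier craving study and adds an allowance for drop-out and for a smaller effect on behavioural measures. With 38–40 per arm and no power calculation for abstinence, precision from data already collected is worth having.

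**Working it through.** **No power figure to reproduce.** The article gives no power, alpha or SD for abstinent days. Its sample size cannot be rebuilt by formula: 30/(1 − 0.10) = 33.3, or 34 per group, and the remaining 4–6 up to 38–40 is an allowance the article does not quantify. What follows is therefore illustrative.

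**Inputs.**
- n = 40 per arm (Power analysis), and 36 per arm after 10% drop-out (40 × 0.90).
- d = 0.48, the article's effect size for craving (Background). It is not an effect on abstinence and is used for scale only.
- Two-sided alpha 5%: assumed.
- rho between the day-1 drinking measure and the outcome: not in the article, assumed 0.2 to 0.5.

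**Formula.** Adjusting for one baseline covariate multiplies the residual variance by 1 − rho², so the effective standardised difference becomes d/√(1 − rho²). Power is that of a two-sample t-test at this difference. At rho 0.4, for example, 0.48/√0.84 = 0.524.

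| rho | Variance factor | Power, 40 per arm | Gain (points) | Power, 36 per arm |
|---|---|---|---|---|
| unadjusted | 1.00 | 56.4% | – | 51.9% |
| 0.2 | 0.96 | 58.1% | 1.7 | 53.6% |
| 0.3 | 0.91 | 60.4% | 4.0 | 55.8% |
| 0.4 | 0.84 | 63.8% | 7.4 | 59.2% |
| 0.5 | 0.75 | 68.7% | 12.3 | 64.0% |

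At rho 0.1 and 40 per arm, power moves only from 56.4% to 56.8%. A gain of 5 points needs rho of about 0.35 (61.9%). Simulating normal data at 36 per arm (3000 runs per rho) gave t-test against ANCOVA power of 0.52 v 0.54, 0.52 v 0.54, 0.53 v 0.58 and 0.51 v 0.63 at rho 0.2, 0.3, 0.4 and 0.5, in line with the table.

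**Chance imbalance is the same quantity.** In SD units, the unadjusted difference has variance 2/n = 2/40 = 0.050. This splits into rho² × 0.050 from random imbalance in baseline drinking and (1 − rho²) × 0.050 from everything else. At rho 0.5 the parts are 0.0125 and 0.0375. The first is exactly the 25% that adjustment removes, and the unadjusted standard error already includes it.

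**Bounded outcome.** Abstinent days lie between 0 and 180, so the normal model is only a guide. Two simulations with assumed distributions address this.
- Latent normal clipped to 0–180, latent effect 0.55 SD, 40 per arm, 4000 runs. Mann-Whitney against rank ANCOVA: 0.63 v 0.63, 0.62 v 0.65, 0.62 v 0.68 and 0.62 v 0.72 at latent rho 0.2, 0.3, 0.4 and 0.5. Type I error was 0.044–0.052.
- Outcome with a ceiling at 180, 36 per arm, 3000 runs:

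| Observed correlation, about | Mann-Whitney | Linear ANCOVA | Rank ANCOVA |
|---|---|---|---|
| 0.18 | 63% | 62% | 65% |
| 0.28 | 64% | 63% | 66% |
| 0.37 | 62% | 65% | 68% |

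The Monte Carlo standard error of each figure is just under 1 point (for example √(0.63 × 0.37/3000) = 0.009), so differences of 1–2 points should not be read closely. The pattern is that below a correlation of about 0.3, linear ANCOVA on raw days gains nothing over a rank test the plan already permits. Rank ANCOVA gains little at low correlation and more as it rises.

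**The case against.** The strongest reply is that the article never says its test is unadjusted, and that a condensed article may leave covariates to a full protocol or SAP. This stands in part: such a document could add them. But the article does fix the class of analysis and the single criterion for choosing within it, and it lists predictors wherever it intends a model. The point addresses that stated choice. It does not show a decision to disregard drinking history.

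A reader might infer that the planned test is biased, or that a chance difference in drinking severity does separate damage to the estimated effect. Neither follows. Under 1:1 randomisation the two-group comparison is unbiased and keeps its type I error, and the imbalance is part of the standard error, as shown above.

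A reader might also infer that the gain is assured. The article does not support that. Nothing in it shows that the day-1 measures predict abstinent days. There is no baseline TLFB, so the outcome itself has no baseline value. Participants are already three to four weeks abstinent at recruitment, which may leave rho low. It also does not show that the adapted history yields a usable figure for recent intake. These objections stand and limit the size of the point.

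**Conclusion.** The point holds as a modest efficiency issue. As written, the main comparisons of abstinent days and total alcohol do not use the drinking measures collected on test day 1. There is no bias and no error in the planned test.

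On the assumptions above, the gain at 40 per arm runs from about 2 points of power at rho 0.2 to about 12 at rho 0.5, and is near zero if rho is lower still. The effect size is borrowed from craving, rho is not documented, and the outcome is bounded, so these figures indicate scale and do not forecast this trial's power. The change is still worth making, because it uses data already scheduled and the sample size has no power basis for the primary outcome.

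**What to change.** Under Statistical analyses, in both Primary outcome measure and Secondary outcome measures, make the main comparison of abstinent days and of total alcohol consumption a covariate-adjusted analysis suited to a bounded, skewed outcome. Rank-based ANCOVA is one option; regression with robust or bootstrap standard errors is another.

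Include one day-1 drinking measure, recorded before the first stimulation: the AUDIT total, or a named quantity from the drinking history if it can be derived. Fix the measure, any transformation and the model before unblinding. Because the trial is single blind, that should mean before any outcome is examined by arm. Put the same covariate in the imputation model for the primary outcome, and keep the unadjusted two-group test as a sensitivity analysis.

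The cost is a change of wording, one degree of freedom out of about 78 (2 × 40 − 2), and the need to choose the covariate in advance. Both measures are already in the schedule, so no new data are needed. The return may be small.

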#### Secondary outcome measures

An appropriate test for comparison of two groups will be used depending on the distribution of the outcome measures ‘days until first relapse’ and ‘total alcohol consumption’.

Multilevel models (capable of handling missing data points) with predictors time, treatment and time X treatment interaction will be used to test for the effect of the HF-rTMS add-on treatment on craving. The following time points will be included: post HF-rTMS, 3 months follow up and 6 months follow up.

#### Additional clinical outcome measures

##### Explorative alcohol use parameters

An appropriate test for comparison of two groups will be used depending on the distribution of the outcome measure ‘full abstinence rate’. An appropriate test for comparing a categorical variable between two groups will be used for the outcome measure ‘treatment success’.

##### Additional craving assessment

Multilevel models (capable of handling missing data points) with predictors time, treatment and time X treatment interaction will be used to test for the effect of the HF-rTMS add-on treatment on craving measured with the OCDS. The following time points will be included: post HF-rTMS, 3 months follow up and 6 months follow up. Data of the VAS scales will be analyzed by calculating difference scores between pre and post HF-rTMS. These scores will be used in a multilevel model (capable of handling missing data points) with predictors time, treatment and time X treatment interaction to test for the effect of the HF-rTMS add-on treatment.

##### Questionnaires

Multilevel models (capable of handling missing data points) with predictors time, treatment and time X treatment interaction will be used to test for the effect of the HF-rTMS add-on treatment on questionnaire scores. Total scores of baseline, intermediate and post-rTMS data will be compared.

##### Supplementary measures

These measures will be compared between groups using an appropriate statistical test depending on the distribution of the outcome measure.

#### Neurocognitive measures

Multilevel models (capable of handling missing data points) with predictors time, treatment and time X treatment interaction will be used to test for the effect of the HF-rTMS add-on treatment on neurocognitive measures. The following time points will be included: baseline, intermediate and post HF-rTMS.

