On a neurobiological level craving is associated with heightened striatal activity related to addiction-relevant stimuli, whereas diminished cognitive control is associated with decreased prefrontal activity [13]. One of the areas involved in cognitive control is the dorsolateral prefrontal cortex (DLPFC) [14]. By stimulating the DLPFC with a high-frequency (10 Hz) protocol, the neural activity of this area is enhanced [15] thereby improving cognitive control [16, 17]. Furthermore, it is known that the prefrontal cortex has abundant connections with the striatum [18]. Indeed neuromodulation of the DLPFC has shown to induce changes in neurotransmitter concentrations in the striatum [19] and can decrease feelings of craving with a medium effect size [d = 0.48] (Jansen et al., 2013). The DLPFC therefore seems an excellent target area for treating alcohol dependence because it could enhance cognitive control functions while also influencing striatal functioning and reducing feelings of craving [5]. However, results of clinical trials investigating the effect of *multiple* HF-rTMS sessions on craving are very scarce and inconsistent, with one study stimulating the right DLPFC that reported reduced craving [20] and one study stimulating the left DLPFC that failed finding an effect on craving [21]. Furthermore no studies thus far investigated the effect of multiple HF-rTMS sessions on abstinence rates after a longer period of time.

Altogether the effect of multiple HF-rTMS sessions on abstinence rates, perceived craving and the neurocognitive and neurobiological working mechanisms are poorly investigated (see also, [22]). The current study aims to elucidate the effect of *multiple* sessions of HF-rTMS on abstinence, craving, cognition and brain functioning. We will conduct a single center, single blind, randomized controlled trial with 80 abstinent alcohol dependent subjects in treatment randomized (1:1) to either treatment as usual (TAU) plus 10 sessions of active HF-rTMS or TAU plus 10 sessions of placebo/ sham HF-rTMS. The effect of active versus sham HF-rTMS treatment will be investigated on measures of abstinence, craving, cognition and brain functioning. We expect higher abstinence rates and decreased perceived craving together with improved functioning on the neurocognitive tasks and brain functioning measures in the active HF-rTMS treated group compared with the sham HF-rTMS treated group.

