#### Neurocognitive measures

Despite the role of the prefrontal cortex in higher cognitive processes [44], the effect of HF-rTMS over the rDLPFC on neurocognitive measures in alcohol dependent individuals is poorly investigated (see also [22]). Therefore the effect of active HF-rTMS compared with sham HF-rTMS on several neurocognitive tasks will be assessed before the first, after the fifth and tenth HF-rTMS session. Neurocognitive tasks will focus on cognitive control and other relevant processes such as approach behavior and working memory. Participants will be situated in front of a finger operated touch screen tablet (Hewlett-Packard; Windows 8.1) on which the tasks will be conducted.Go/ No-go Task (GNGT): This task (adapted from [45]) measures the ability to refrain from action initiation [46]. Participants see a number (‘1’, ‘2’, ‘3’, ‘4’, ‘5’, ‘6’, ‘7’, ‘8’, ‘9’) projected on a screen in front of them. They are instructed to press the spacebar with their right hand as soon as they see a number, but not if it is the number ‘3’ (=no-go trial) (Fig. 2a). The outcome measure will be the number of commission errors, i.e. a response to a no-go trial, reflecting action impulsivity. The higher the number of commission errors, the more impulsive an individual is.Approach Avoidance Task (AAT): This task (adapted from [47]) measures the bias towards approaching alcoholic beverages. During this task pictures from a validated dataset [48] of alcoholic beverages, sodas and neutral objects (for example scissors) are presented on a screen in front of the participant. The pictures are rotated 3° towards the left or right, indicating whether a participant has to pull or push a picture using a joystick (Fig. 2b). When a picture is pulled or pushed the size of the picture increases or decreases respectively. The bias score per stimulus category [alcohol/ soda/ neutral] will be calculated by subtracting the median reaction time of the approach (pull) trials from the median reaction time of the avoid (push) trials. When the result of this subtraction is positive, this indicates a relative faster approach compared to avoid, i.e. an approach bias. When the result of the subtraction is negative this indicates a relatively faster avoid compared to approach, i.e. avoid- bias.Delay Discounting Task (DDT): This task (based on [49]) measures the extent of impulsive decision making. Participants are presented with a choice between an immediate (lower) and a delayed (higher) hypothetical monetary reward (Fig. 2c). The value of the immediate reward varies across the trials in one block, and depends on the responses that are made [49]. The outcome measure will be the area under the discounting curve (AUC), reflecting the degree of discounting by delay [50]. Impulsive choice behavior is indicated by a smaller AUC.Spatial Working Memory Task (SWMT): This task is part of the Cambridge Neuropsychological Test Automated Battery (CANTAB) test battery, and measures the ability of a subject to remember spatial information and manipulate this using working memory. During this task participants are presented with a number of colored squares (or boxes for the participant) shown on a screen. The participant is instructed to find a blue token hidden in each box, and use this token to fill up the black empty space on the right side of the screen (Fig. 2d). In order to open a box, and see whether there is a hidden token inside, the participant needs to touch the box on the screen. If no token is found the participant must continue its search until a token is found. When there is a blue token inside, the participant must now touch the black empty space to fill up this space with the token. Now the participant has to begin a new search. The next token will only be hidden in a box that so far has been empty. This procedure is repeated until all tokens are found and the entire empty space is filled with tokens. The task starts with three boxes, and this will increase to four, six and eight boxes. Touching a box where the token had already been found is considered an error. The outcome measure will be the number of errors a subject makes and reflects working memory capacity. The more errors a subject makes, the lower the working memory capacity.Stop Signal Task (SST): This task (part of the CANTAB test battery) measures the ability of an individual to inhibit an ongoing action [46]. Participants are presented with a white ring on a black screen. In the ring a white arrow pointing either to the left or to the right appears. The participant needs to press the left button if the arrow points to the left and the right button when the arrow points to the right as fast as possible (go trial). During some trials the participant hears an auditory signal (beep), after the arrow appears, which indicates they have to stop their response and not press the button (stop trial) (Fig. 2e). The outcome measure will be the amount of successful stops and reflects the capability of stopping an initiated response. The lower the number of successful stops, the more impulsive an individual is.Intra-dimensional/ Extra- dimensional Set Shift (IDED): This task (part from the CANTAB test battery) tests rule acquisition and reversal learning. Two stimuli are presented on a screen from which the participant has to choose one by pressing on the screen. These stimuli are made up of two artificial dimensions: color-filled shapes and/or white lines. The stimuli presented can be either simple (just one of the two dimensions) or compound (stimuli contain both the dimensions). The task contains 9 blocks increasing in difficulty (Fig. 2f). After pressing the stimulus on the screen the computer gives feedback on whether this was the correct stimulus. In this way participants can learn the task rules. After six correct responses (learning criterion) the program changes the rule, and thereby the participant reaches the next block. If the participant does not reach the learning criterion the test terminates after 50 trials. The outcome measures will be the number of trials needed to reach the next stage (indicating the rule learning capacity), and the number of errors made after a rule change (indicating the capacity of reversal learning) [51]. Higher numbers indicate lower rule learning and reversal learning capacity.

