## Discussion

This paper presents a single blind randomized clinical trial protocol investigating whether 10 sessions of active HF-rTMS compared with 10 sessions of sham HF-rTMS improve the treatment outcomes of alcohol dependence. The aim of this study is to increase abstinence rates, decrease craving, and improve neurocognitive and brain functioning measures relevant for alcohol dependence treatment.

The main challenge of this study will be completion of the entire follow-up procedure. Participants will be called three, six and twelve months after finishing the last stimulation session to assess the number of abstinent days. Within the population of alcohol dependent individuals, chances are high that participants will get lost at follow-up [62]. There is a risk that we may not get the primary outcome measure for all participants, because it is uncertain whether we can reach all participants at six months follow-up. However, our research group is experienced with a six months follow-up and no main problems have been reported in reaching participants.

The first strength of this study is that it investigates the effect of *multiple* HF-rTMS session. The second strength of this study is that it takes into account several aspects that are important in the treatment of alcohol dependence. So far studies mainly looked at the effect of HF-rTMS on self-reported craving, although the most relevant clinical question is whether HF-rTMS has an effect on abstinence [22]. This study will perform follow-up measurements to assess the number of abstinent days in the six months after the last neurostimulation session. Furthermore this study will elucidate the underlying mechanism by which rTMS may induce its effects in alcohol dependent individuals by investigating several neurocognitive as well as neuroimaging measures [22].

The limitation of this study is that the trial is not double blind controlled. However, a double blind controlled rTMS study with a sham condition similar to this study is impossible because the researcher needs to tilt the coil 90° relative to the skull [23]. Because this study only uses participants self-report measures and the researcher does not score any clinical effects, the outcome measures are not affected by the knowledge of the researcher, and a double blind paradigm is not necessary.

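### The neurocognitive and questionnaire models count the pre-stimulation baseline as an outcome visit, so their treatment term is not a treatment effect, and no deciding term is named

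*Protocol article*

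**What the plan says.** Under Statistical analyses, Neurocognitive measures, the article plans multilevel models "with predictors time, treatment and time X treatment interaction will be used to test for the effect of the HF-rTMS add-on treatment on neurocognitive measures". It lists three visits: baseline, intermediate and post-stimulation. The outcomes section of the same name places these assessments before the first session and after the fifth and tenth.

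The Questionnaires analysis section uses the same three predictors and adds: "Total scores of baseline, intermediate and post-rTMS data will be compared".

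The sections on secondary outcomes (AUQ craving) and additional craving assessment (OCDS) use the same model description, but with post-stimulation, three-month and six-month visits only.

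None of these sections says which term decides. The Background states a directional expectation of "improved functioning on the neurocognitive tasks and brain functioning measures in the active HF-rTMS treated group compared with the sham HF-rTMS treated group".

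**The concern.** A randomised arm difference at a visit before stimulation can only be chance. If that visit is one of the outcomes, a term described as testing the effect of stimulation partly or wholly measures something stimulation cannot have changed. In the craving models every visit follows stimulation, so the treatment term there is a legitimate arm difference. The same description thus carries a valid test in one place and an invalid one in another, and the article does not mark the change.

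At stake is how the cognitive and questionnaire results are read. An analyst quoting the treatment term could miss a real effect or report a baseline imbalance. One quoting the interaction could reach the opposite conclusion from the same data. The Discussion says "this study will elucidate the underlying mechanism by which rTMS may induce its effects in alcohol dependent individuals", partly on the strength of these measures, so the choice of term has consequences for interpretation.

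**Working it through.** The article gives no significance level, effect size or power for these outcomes, so there is no figure of its own to reproduce. The check has two steps.

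**Step 1: what each term estimates.** Let the true active-sham difference be 0 at baseline and d after sessions 5 and 10.

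- Treatment term, baseline as reference visit: expected value 0 whatever d is. It tests the baseline imbalance, so its chance of significance stays at the test level.
- Treatment term averaged over the three visits: (0 + d + d)/3 = 2d/3, so a third of the effect is lost.
- Time x treatment (two degrees of freedom): tests whether the arm difference changes across visits, so it does respond to d.
- Post-stimulation difference with baseline as covariate: estimates d.
- AUQ and OCDS models: no untreated visit enters, so the treatment term is a valid arm difference.

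**Step 2: what the choice costs.** The 40 per arm is the upper end of the 38–40 per group in the Power analysis section. The following are assumptions: SD 1 at each visit, d = 0.5 SD at both later visits, equal correlation r between visits (0.5 or 0.7), 5% two-sided, normal approximation.

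For single contrasts, SE = sqrt(2 × variance / 40), z = effect / SE, and power is approximately Φ(z − 1.96).

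| Test | Effect | Variance | z at r = 0.5 / 0.7 | Power at r = 0.5 / 0.7 |
|---|---|---|---|---|
| Averaged treatment term | 0.333 | (1 + 2r)/3 = 0.667 / 0.800 | 1.83 / 1.67 | 45% / 38% |
| Session 10, baseline as covariate | 0.5 | 1 − r² = 0.750 / 0.510 | 2.58 / 3.13 | 73% / 88% |
| Mean of sessions 5 and 10, baseline as covariate | 0.5 | (1 + r)/2 − r² = 0.500 / 0.360 | 3.16 / 3.73 | 89% / 96% |

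For the interaction, the arm differences (0, 0.5, 0.5) have a sum of squares about their mean of 0.25 × 2/3 = 0.167. The noncentrality is (40/2) × 0.167 / (1 − r) = 6.67 at r = 0.5 and 11.11 at r = 0.7. Against a chi-square on two degrees of freedom (critical value 5.99), power is 63% and 86%.

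**Baseline as covariate versus change from baseline.** For session 10 alone, the change score has variance 2 − 2r = 1.00 / 0.60, giving z = 2.24 / 2.89 and power 61% / 82%, against 73% / 88% with baseline as covariate. The two are not equivalent, and the covariate form is more precise.

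**Sensitivity to drop-out.** The Power analysis section allows for 10% drop-out. With 40 × 0.9 = 36 per arm, the same formulas give 41% / 35% (averaged term), 58% / 82% (interaction), 69% / 84% (adjusted, session 10) and 85% / 94% (adjusted, mean of both visits). The order is unchanged.

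**The case against.** The strongest reply is that the article lists predictors, not tests. A model with an interaction ordinarily carries its lower-order terms, and with baseline included a competent analyst would read time x treatment. The Questionnaires sentence about comparing the three visits points the same way. This stands in part: nothing in the article says that the treatment main effect will be quoted. But the text presents the model as a whole as the test of the effect, and it uses the same description for the craving models, where the main effect is the natural term to read. The intended term cannot be recovered from the text. Even on the charitable reading, the interaction is not the most precise test of the data being collected.

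It is also fair that these are ranked as additional research questions in Aims of the study, and that the Discussion ties further trials to abstinence, craving and side effects. That limits the importance of the point.

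A reader might go further and infer that the several task scores, each with two treatment terms, are to be tested without any multiplicity control, so that a false mechanistic finding is likely. The documents do not support this. The article's one mention, "if required, multiple comparison corrections will be performed", concerns descriptive comparisons and does not exclude correction elsewhere. A condensed article may leave the handling of additional outcomes to a full protocol or analysis plan, which is not shown. Any family-wise error figure would also rest on a significance level and a correlation between tasks that the article does not give.

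**Conclusion.** The point holds as a fault in the stated model. In the neurocognitive and questionnaire analyses the treatment term is either the baseline imbalance or two thirds of the true effect, and no deciding term is named.

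Under the stated assumptions, relying on the averaged treatment term leaves power at about 38–45%, where a baseline-adjusted contrast on the same data would give 73–96%, depending on the visit correlation and on whether one or both later visits are used. The interaction is a valid test and lies at 63–86%. At either correlation it falls below both baseline-adjusted contrasts. The exact percentages depend on the assumed effect and correlations. That the treatment term is not a treatment effect does not.

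The primary abstinence comparison and the AUQ and OCDS models are unaffected. The finding does not extend to a claim that multiplicity is uncontrolled.

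**What to change.** In the Neurocognitive measures and Questionnaires analysis sections:

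- Make the deciding test the active-sham difference after stimulation, with the baseline score as a covariate. State in advance whether this is the session-10 value or the mean of the values after sessions 5 and 10.
- State that no conclusion will be drawn from the treatment main effect in any model that keeps baseline as an outcome visit.
- If the three-visit model is kept, name time x treatment as its test of the stimulation effect, and do not describe it as equivalent to the baseline-adjusted contrast.

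The cost is a few sentences of analysis wording. All the data are already scheduled, and neither the sample size nor the visits change. Choosing between the two post-stimulation contrasts involves a trade-off: the mean of both visits is more precise if the effect is present by session 5, whereas the session-10 value targets the completed course directly.
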